### Sample size

According to Polit and Beck [42], when using ANOVA to compare the means of multiple groups, the simplest method to calculate the sample size is to estimate the ratio of the sum of squared deviations between the groups and the sum of squared deviations of the total (eta-squared, *η*2). However, when there is no experimental result of the same kind of study to base *η*2, the researcher can predict whether the study effect is large, medium, or small. According to the convention, ANOVA is used to compare the means of the smartwatch group, wristband group, and control group. The *η*2 values of large, medium, and small effects are 0.14, 0.06, and 0.01, respectively. The corresponding sample sizes of the three groups are 22, 53, and 319, and the sample size of each group is 22, 53, and 319 when *α* = 0.05 and *β* = 0.02, respectively. Because there were no suitable previous research results as the basis for calculating sample size by formula, the sample size is determined by the estimation method. Taking *α* = 0.05 and *β* = 0.02, the effect is estimated to be medium, and the number of samples in each group is 53. Considering the loss of samples and other reasons to increase the sample content by 15%, we finally included 61 cases in each group for a total of 183 subjects.

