### Evaluation methods

An assessor-blind method is used; that is, questionnaire collectors are research assistants who are trained in the use of measurement tools but are blinded to the grouping of study subjects. The intervention effects of the three groups of patients will be measured at baseline and 2 months, 3 months, and 6 months after discharge. The evaluation content includes questionnaire surveys and biochemical index measurements. Baseline data (during hospitalization) collection: Patients will complete the assessment at the nurses’ station. Follow-up data (after discharge from the hospital) will be collected as follows: The research assistant will visit the patient at home for data collection. Patients will complete the assessment independently, but those with reading difficulties, visual impairment, or handwriting difficulties will be instructed to complete the questionnaire as each item is read to them in neutral, noncryptic language. After the evaluation, the researchers will check whether the evaluation is complete. If there are missing items, patients will complete the items on the spot and return the evaluation for verification again. Any doubts about the content will be verified with the patient on the spot. Upon completion of data collection at each follow-up time point, each study patient will receive a gift for participating in the study. Basic demographic data will be collected at baseline, including age, sex, ethnicity, education level, marital status, job status, family status, and medical condition.1. Primary outcome (for patients)

The primary outcomes are neurological function status, self-management behavior, quality of life, biochemical indicators, recurrence rate, and unplanned readmission rate.

Neurological status

The National Institutes of Health Stroke Scale (NIHSS) is the most common stroke evaluation index in the world. It covers the anterior and posterior circulation of the brain, including consciousness, movement, sensation, speech, and visual field, with a total of 15 items. NIHSS scores range from 0 to 42, with higher scores indicating more severe neurological impairment [43]. Cai Yefeng et al. introduced the NIHSS in China to conduct a multicenter and large sample test, and the results showed that the Chinese version of the NIHSS had good reliability, validity, and sensitivity [44].

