The SPSS 22.0 statistical analysis software will be used to analyze the data, and *P* < 0.05 (two-sided test) will be considered statistically significant. Count data are described by frequency/constituent ratio, and measurement data are described by mean/standard deviation according to the results of the normality test. Pearson’s chi-square test will be used to compare the count data between groups. One-way analysis of variance will be used to compare the measurement data between the three groups, and the Bonferroni method will be used for further comparison between the two groups. Repeated measures analysis of variance will be used to compare the longitudinal changes in indicators with a normal distribution. If the covariance matrix of the observed values at each time point is symmetric or spherical (Mauchly’s test, *P* ≥ 0.05), no correction will be needed. If the covariance matrix of the observed values at each time point is *P* < 0.05 (Mauchly’s test), the Greenhouse‒Geisser correction test will be used.

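### Continuous outcomes are compared by one-way ANOVA without their baseline values, which costs precision that the T0 data would give at no extra cost

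*Protocol article*

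**What the plan says.** The protocol article, under Data management and statistical analysis, names the between-group test for continuous data: "One-way analysis of variance will be used to compare the measurement data between the three groups". The pairwise step follows directly: "the Bonferroni method will be used for further comparison between the two groups". A second method is then added: "Repeated measures analysis of variance will be used to compare the longitudinal changes in indicators with a normal distribution", with a Greenhouse-Geisser correction if Mauchly's test is significant. Baseline is not named as a covariate anywhere, and neither ANCOVA nor a change score is mentioned.

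Under Evaluation methods the schedule reads: "The intervention effects of the three groups of patients will be measured at baseline and 2 months, 3 months, and 6 months after discharge". So the continuous primary measures (NIHSS, MBI, SSBR, SF-12, blood pressure, glucose) have a T0 value.

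The Sample size section rests on the same unadjusted ANOVA. It lists eta-squared values for large, medium and small effects ("effects are 0.14, 0.06, and 0.01, respectively"), chooses the medium one ("Taking *α* = 0.05 and *β* = 0.02, the effect is estimated to be medium") and concludes that "the number of samples in each group is 53", raised to 61 for losses.

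**The concern.** A one-way ANOVA has group as its only factor, so by definition it leaves out the T0 value of the score. If a patient's T0 score predicts the later score, the variation it explains stays in the error term. The group differences and their Bonferroni contrasts then have wider confidence intervals than the collected data require.

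What is at stake is precision. The trial is sized for a medium effect assumed by convention, with no earlier study behind it, so a smaller true effect is quite possible and the spare precision would be useful. The point concerns the continuous patient scores only. Recurrence and unplanned readmission are count data with no baseline value.

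**Working it through.** **Inputs from the article.** Three groups, 1:1:1; two-sided alpha 0.05; eta-squared 0.06; 53 per group before losses and 61 after.

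**Assumed input.** The correlation ρ between the T0 score and the follow-up score is not in the article. I use 0.3, 0.5 and 0.7, with 0.1 as a low case.

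**Step 1: the article's own figure.** With f² = η²/(1 − η²) = 0.06/0.94 = 0.0638 and N = 159, the noncentrality is 159 × 0.0638 = 10.15 on 2 and 156 degrees of freedom. Power is 81.4%. At 61 per group (N = 183) the noncentrality is 11.68 and power is 86.8%. The printed beta of 0.02 does not give 53: it would need 100 per group. A beta of 0.20 gives 52, close to the printed 53. I therefore take 81.4% as the starting power; the printed beta is a separate matter.

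**Step 2: baseline adjustment at one visit.** ANCOVA multiplies the residual variance by 1 − ρ², so the standard error is multiplied by √(1 − ρ²) and the noncentrality is divided by 1 − ρ². One error degree of freedom is lost.

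| ρ | 1 − ρ² | SE ratio | Noncentrality, 53/group | Power, 53/group | Power, 61/group |
|---|---|---|---|---|---|
| none (planned ANOVA) | 1 | 1 | 10.15 | 81.4% | 86.8% |
| 0.1 | 0.99 | 0.995 | 10.25 | 81.8% | 87.2% |
| 0.3 | 0.91 | 0.954 | 11.15 | 85.1% | 89.9% |
| 0.5 | 0.75 | 0.866 | 13.53 | 91.4% | 94.8% |
| 0.7 | 0.51 | 0.714 | 19.90 | 98.3% | 99.3% |

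**Step 3: one Bonferroni pair.** If the third group lies midway between the two extreme groups, eta-squared 0.06 corresponds to d = √0.0638 × √6 = 0.62 between the extremes. At alpha 0.05/3 and 53 per group, power is 78.6% unadjusted and 82.8%, 90.1% and 98.1% adjusted at ρ = 0.3, 0.5 and 0.7.

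**Step 4: does the repeated measures ANOVA already do this?** I assume T0 is one of its four levels, all visits are equally correlated, and the effect is constant after T0. The relevant group-by-time contrast is then the follow-up mean minus T0. In units of the single-visit variance:

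- change contrast: (1 + 2ρ)/3 + 1 − 2ρ
- ANCOVA on the same follow-up mean: (1 + 2ρ)/3 − ρ²

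The difference is 1 − 2ρ + ρ² = (1 − ρ)², which is never negative.

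| ρ | Change contrast | ANCOVA, same visits |
|---|---|---|
| 0.3 | 0.93 | 0.44 |
| 0.5 | 0.67 | 0.42 |
| 0.7 | 0.40 | 0.31 |

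The omnibus group-by-time test (6 and 468 degrees of freedom; noncentrality 159 × 0.0638 × 0.75/(1 − ρ) = 10.87, 15.22 and 25.37) has power 68%, 84% and 98%. Single-visit ANCOVA has 85%, 91% and 98%.

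**The case against.** **The repeated measures ANOVA uses baseline.** This stands in part. Group-by-time draws on each patient's T0 value, so the gain in Step 2 is measured against the one-way ANOVA and is not the loss of the plan as a whole. At ρ = 0.7 the omnibus interaction test already reaches 98%. At ρ = 0.5 and 0.7 the averaged change contrast (0.67 and 0.40) is more precise than ANCOVA at one visit (0.75 and 0.51), although the article does not name that contrast. The gap is not closed, however: the method is limited to normally distributed indicators, the Bonferroni step is attached to the one-way ANOVA, and on the same follow-up visits adjustment is never less precise.

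**The correlation is unknown.** This stands. Wide entry on the Barthel Index (above 40, no upper limit) bears directly on MBI only. T0 is taken in hospital and follow-up at home, so for SSBR, blood pressure and glucose the correlation may be low.

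**Covariates may be left to a fuller document.** This does not remove the point, because the article names a test that has no covariate and sizes the trial on it.

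**Stronger readings that the document does not support.**
- A reader might infer that the planned test is biased or invalid. It is neither: randomisation protects it, and its standard error already reflects chance baseline imbalance.
- A reader might infer that a repeated measures main effect including T0 shrinks the treatment effect to three quarters. That arithmetic holds for a constant post-baseline effect, but the article never names the group main effect as its efficacy test.
- A reader might infer that raw scores are meant, that T3 is the key visit, or that baseline differences will be tested for significance. The article states none of these. If change scores were meant, ANCOVA would still be at least as precise.

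**Conclusion.** The point holds as a loss of efficiency for the continuous outcomes. Against the named one-way ANOVA, adjustment for T0 narrows the standard error of a single-visit comparison by 5%, 13% or 29% and raises omnibus power at 53 per group from 81% to 85%, 91% or 98%. These figures rest on assumed correlations of 0.3, 0.5 and 0.7, on eta-squared 0.06 and on reading the design power as about 80%. At a correlation of 0.1 power moves only from 81.4% to 81.8%. For normally distributed indicators the repeated measures ANOVA already recovers part of the gain. The change is worth making because adjustment costs one degree of freedom and can hardly lose precision.

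**What to change.** For continuous outcomes, replace the one-way ANOVA with ANCOVA at each follow-up visit, or with a mixed model in which only the follow-up visits are outcomes. In either case name the T0 value of the same score as a prespecified covariate, and take the Bonferroni pairwise contrasts from that model. Hospital may be added as an optional covariate; the article describes no stratification by hospital, and no gain from this has been quantified. The tests for recurrence and readmission stay as they are.

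The cost is a change of wording. The T0 data are already scheduled, and the planned software (SPSS) fits these models. The Trial status section says that recruitment had not started at submission; if outcome data have been seen since, the date of the change should be recorded.

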## Methods

### Study design

This study is a parallel-group randomized controlled trial with a 1:1:1 randomization scheme that will be conducted in West China Hospital of Sichuan University and Chengdu Second People's Hospital from April 2023 to April 2024. In this study, the Real-time and Individualized Self-management Support (RISS) program will be developed for stroke survivors guided by resilience theory. Patients will wear smartwatches (MLY B10, Huawei wrist electrocardio-blood pressure record) that can collect real-time data such as exercise, sleep, blood pressure, heart rate, and blood oxygen to prompt self-management support for transitional stroke patients. Our hypothesis is that compared with the wristband group and control group, stroke patients who receive the RISS program will have a lower incidence of recurrence rate and an improved quality of life. This study could provide new ideas for increasing patients’ self-management ability, improving quality of life, and optimizing disease outcomes. This trial protocol uses the Standard Protocol Items: Recommendations for Interventional Trials (SPIRIT) reporting guidelines (see Additional file 2). The research method conforms to the joint standard of multiarm test reports. A summary of the study design is shown in Fig. 1. Schedule of enrollment, interventions, and assessments is shown in Fig. 2.

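### Bonferroni after the three-group ANOVA is valid but more conservative than needed: a closed test or Holm holds the same 5% per outcome and visit with more power

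*Protocol article*

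**What the plan says.** Under *Data management and statistical analysis* the protocol article states: "One-way analysis of variance will be used to compare the measurement data between the three groups", and then "the Bonferroni method will be used for further comparison between the two groups". Significance is set at two-sided 0.05. The text does not give the Bonferroni divisor, and it does not say whether pairs are tested only after a significant F. Count data go to Pearson's chi-square with no pairwise rule attached. Longitudinal change goes to repeated measures ANOVA.

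Under *Study design* the hypothesis names two comparators: "compared with the wristband group and control group, stroke patients who receive the RISS program will have a lower incidence of recurrence rate" and better quality of life. The conclusion therefore rests on pairwise comparisons.

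Under *Sample size* the trial is sized on the three-group F test alone. The eta-squared "values of large, medium, and small effects are 0.14, 0.06, and 0.01, respectively"; the medium value is chosen, "the number of samples in each group is 53", and 15% is added to reach 61.

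**The concern.** The hypothesis needs RISS against wristband and RISS against control, but the sample size secures power only for the overall F test. Any avoidable loss at the pairwise step falls on the comparisons that carry the conclusion. Dividing 0.05 by three is one such loss, because with three groups a less strict rule holds the same 5% limit. What is at stake is power at a fixed sample size, not the validity of the plan.

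**Working it through.** **Inputs from the protocol article.** Three groups, 1:1:1; two-sided 0.05; eta-squared 0.06; 53 evaluable and 61 enrolled per group.

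**Assumptions.** Bonferroni is taken over the three pairs (0.05/3 = 0.0167) after a significant F. Outcomes are normal with equal variance. The pattern of means is not given, so two patterns are used.

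**1. The plan's own figure.** Noncentrality = N × eta²/(1 − eta²) = 159 × 0.06/0.94 = 10.15, on 2 and 156 degrees of freedom. Power of the F test at 53 per group is 81.4%; 80% needs 52. So 53 fits beta = 0.20. The printed beta of 0.02 would need 100 per group. That discrepancy is a separate matter and does not affect this point. The inflation reproduces: 53 × 1.15 = 60.95, rounded up to 61.

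**2. Converting eta-squared to differences in SD units.** f = √(0.06/0.94) = 0.2526.
- Only RISS differs: means (d, 0, 0), f = d√2/3, so d = 0.536.
- Equally spaced: means (d, d/2, 0), f = d/√6, so d = 0.619 and d/2 = 0.309.

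**3. Why the closed test holds 5%.** The hypotheses are the three pairwise equalities. Any two of them together imply that all three means are equal, so the only intersection hypothesis is the global null, which the F test examines at 5%. Rejecting a pair only if both the F test and that pair's own test are significant at 5% is therefore a closed procedure. With four or more groups this would fail. Holm needs no F test, holds 5% and rejects everything that Bonferroni rejects.

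**4. Simulation.** 1,000,000 replicates per scenario, pooled variance on 3n − 3 degrees of freedom.

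| Scenario and quantity | F + Bonferroni | Holm | Closed test |
|---|---|---|---|
| n = 53, only RISS differs: one given RISS comparison | 63.2% | 66.6% | 73.6% |
| n = 53, only RISS differs: both RISS comparisons | 47.9% | 54.4% | 65.8% |
| n = 53, equal spacing: RISS v wristband | 20.8% | 26.5% | 34.6% |
| n = 53, equal spacing: RISS v control | 77.3% | 78.4% | 80.7% |
| n = 53, equal spacing: both RISS comparisons | 19.8% | 25.8% | 34.2% |
| n = 61 (no dropout), only RISS differs: both | 56.6% | 63.1% | 73.5% |
| Family-wise error, all means equal, n = 53 | 4.2% | 4.4% | 5.0% |
| Family-wise error, only wristband = control true, very large RISS effect, n = 53 | 1.7% | 5.0% | 5.0% |

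Gain for both comparisons at n = 53, only RISS differing: 65.8 − 47.9 = 17.9 points (closed) and 54.4 − 47.9 = 6.5 points (Holm). With equal spacing: 34.2 − 19.8 = 14.4 and 25.8 − 19.8 = 6.0 points.

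**5. Sensitivity to the divisor.** If Bonferroni were applied only to the two RISS comparisons (0.025 each, after a significant F), power for both at n = 53 with only RISS differing would be 54.6%. The gain from the closed test would then be 65.8 − 54.6 = 11.2 points.

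**The case against.** Bonferroni is a legitimate choice. It controls the family-wise error, it is simple, and it comes with matching simultaneous confidence intervals, which the closed test and Holm do not supply directly. Nothing in the statistical section is contradicted. That stands: this is an efficiency suggestion, not an error in the plan.

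A reader might infer that the division by three buys no protection at all. The figures do not support that. When only wristband and control are equal and RISS has a very large effect, F plus Bonferroni falsely separates them 1.7% of the time, against 5.0% for the closed test. The extra protection is real; it is just not needed to reach 5% across three pairs.

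A reader might also infer that the closed test keeps 5% for the trial as a whole. It does not. The article names six primary outcomes measured at several visits, and its statistical section states no adjustment across them. If, purely for illustration, six independent outcomes are each analysed once and only wristband = control is true, the chance of at least one false wristband-control claim is 1 − 0.983⁶ ≈ 10% with F plus Bonferroni and 1 − 0.95⁶ ≈ 26% with the closed test. Bonferroni over pairs was not designed to cover this, but a change that relaxes the only stated adjustment has to say so.

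Finally, the divisor of 3 and the patterns of means are assumptions, and the size of the gain depends on both.

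**Conclusion.** The point holds as a low-cost improvement for continuous outcomes, per outcome and time point. At 53 per group and eta-squared 0.06, with a divisor of 3, the closed test raises power to show RISS different from both comparators by about 14 to 18 points over F plus Bonferroni. With a divisor of 2 the gain is about 11 points if only RISS differs. Holm adds about 6 points for both comparisons. For a single comparison Holm adds about 3 points if only RISS differs; with equal spacing it adds about 6 for RISS against wristband and about 1 for RISS against control. Large gains belong to the closed test only.

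Two further inferences should be resisted. The power figures say nothing about recurrence, which is count data under the chi-square test, and they were not computed for the repeated measures analysis. Nor does the change rescue the hypothesis: with equally spaced means even the closed test reaches only about 34% for both comparisons, because the trial is sized on the overall F test.

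**What to change.** In *Data management and statistical analysis*, for continuous outcomes, replace the Bonferroni clause with a rule such as: for each outcome and time point the three groups are compared by the F test at 0.05; if it is significant, each pair is tested at two-sided 0.05, and if not, no pair is declared different; this is a closed test, valid because there are exactly three groups. If a stand-alone procedure is preferred, name Holm over the three pairs and accept the smaller gain.

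Add that the 5% applies per outcome and time point and does not address multiplicity across the six primary outcomes. Bonferroni-adjusted intervals may be reported alongside, with a note that such an interval can include zero for a pair that the closed test declares different. If Bonferroni is kept for its intervals, state the divisor.

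The cost is a few lines of text and no patients. The downsides are less direct simultaneous intervals, less protection for wristband against control when RISS works, and a rule that lapses if the number of groups changes. The article says recruitment had not started when the protocol was submitted, so on its face the rule could be fixed before any data existed.

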**Methods:**

This parallel-group randomized controlled trial will be conducted in two hospitals and patients’ homes. A total of 183 adult stroke patients will be enrolled in the study and randomly assigned to three groups in a 1:1:1 ratio. The smartwatch intervention group (*n* = 61) will receive Real-time and Individualized Self-management Support (RISS) program + routine care, the wristband group (*n* = 61) will wear a fitness tracker (self-monitoring) + routine care, and the control group (*n* = 61) will receive routine stroke care. The intervention will last for 6 months. The primary outcomes are neurological function status, self-management behavior, quality of life, biochemical indicators, recurrence rate, and unplanned readmission rate. Secondary outcomes are resilience, patient activation, psychological status, and caregiver assessments. The analysis is intention-to-treat. The intervention effect will be evaluated at baseline (T0), 2 months after discharge (T1), 3 months after discharge (T2), and 6 months after discharge (T3).

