### Recruitment

The recruitment sites for this research are the departments of neurology, West China Hospital of Sichuan University and department of neurology, Chengdu Second People's Hospital. They are all in Chengdu, Sichuan province, China. Each day from 15:00 to 17:00, the research assistants will go to the nurses’ station to collect the basic information of patients who are going to be discharged the next day and screen patients according to the inclusion and exclusion criteria. Then, the research assistants will invite the patients to the nurse station for communication and explain the purpose, significance, specific implementation process, and precautions of the project and invite patients to participate in this study. After obtaining the patient’s consent, the research assistant will record the patient’s basic information (i.e., name, sex, age, disease condition) and contact information and invite patients to join the study’s WeChat group. For the purpose of intention-to-treat analysis, if a participant drops out of the study, the research assistant will also record their basic information and the reasons for withdrawal for comparison with the enrolled participants.

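### The repeated-measures ANOVA planned for normally distributed outcomes drops anyone who misses a visit, so that comparison is complete-case and conflicts with the intention-to-treat claim

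*Protocol article*

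**What the plan says.** The Methods part of the abstract states: "The analysis is intention-to-treat". The Recruitment section gives the only provision tied to that principle: "For the purpose of intention-to-treat analysis, if a participant drops out of the study, the research assistant will also record their basic information". It adds the reasons for withdrawal, and says that the purpose is to compare these people with those enrolled.

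Under Data management and statistical analysis, the longitudinal method is fixed: "Repeated measures analysis of variance will be used to compare the longitudinal changes in indicators with a normal distribution". If Mauchly's test gives P of at least 0.05, "no correction will be needed"; otherwise the Greenhouse-Geisser correction applies. The software is also fixed: "The SPSS 22.0 statistical analysis software will be used to analyze the data".

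The same section names two methods that are not longitudinal: "One-way analysis of variance will be used to compare the measurement data between the three groups", followed by Bonferroni comparisons, and, for categorical outcomes, a Pearson "chi-square test will be used to compare the count data between groups".

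Evaluation methods sets four assessments: baseline, then 2, 3 and 6 months after discharge (T0 to T3). Missing questionnaire items are completed on the spot during a visit. The article gives no rule for a visit that does not take place.

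The Sample size section expects some loss: "Considering the loss of samples and other reasons to increase the sample content by 15" per cent, which takes 53 per group to 61. Ethics and dissemination lets patients withdraw at any stage and has the study leader end a patient's participation when that patient becomes sicker.

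**The concern.** The claimed population and the named method do not fit together. Mauchly's test and the Greenhouse-Geisser correction identify the classical repeated-measures procedure, not a mixed model. In SPSS that procedure works on one row per participant and deletes the whole row if any visit is empty. A patient assessed at T0, T1 and T2 who is lost before T3 contributes nothing.

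Two things are at stake. First, outcome values already collected at T1 and T2 are discarded from this analysis. Second, the remaining participants may be a selected group. Deterioration is itself a stated reason for ending participation, and the outcomes analysed in this way may include neurological status, daily function and quality of life. If deterioration is less common in one arm, the completers in the three arms are no longer comparable in the way that randomisation made them.

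**Working it through.** **1. Which analyses need all visits**

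| Analysis in the article | Needs a value at every visit? |
|---|---|
| Repeated-measures ANOVA, normally distributed indicators | Yes |
| One-way ANOVA with Bonferroni comparisons | No, only the visit analysed |
| Pearson chi-square, count data | No |

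The conflict is confined to the first row.

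**2. Does anything in the article bring dropouts back in?** The Recruitment provision collects their basic information and reasons. That describes them but supplies no outcome value and no rule for using earlier values. The on-the-spot checks concern missing items within an attended visit. The double data entry concerns transcription. None of these covers a missed visit.

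**3. The plan's own sample size.** The inputs from the Sample size section are η² = 0.06, α = 0.05 and three groups. With f² = η²/(1 − η²) = 0.06/0.94 = 0.0638, and one-way ANOVA power from the noncentral F distribution with noncentrality 3n·f²:

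- 52 per group: power 0.806
- 53 per group: power 0.814
- 61 per group: power 0.868

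The smallest n for 80% power is 52, against the stated 53, so the figure reproduces at β = 0.20. The printed β of 0.02 would need 100 per group; that mismatch is a separate matter. The inflation is 53 × 1.15 = 60.95, rounded up to 61, which also reproduces.

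**4. Loss that the inflation tolerates.** 61 − 53 = 8 per group. 8/61 = 13.1%, and 3 × 8 = 24 of 183.

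**5. Loss under listwise deletion.** The article gives no missed-visit rate, so these rates are assumptions. Suppose each of the three follow-up visits is missed independently with probability m, and baseline is complete because it is collected in hospital. The share excluded is 1 − (1 − m)³.

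- m = 5%: 1 − 0.95³ = 14.3%, leaving 183 × 0.857 = about 157
- m = 10%: 1 − 0.90³ = 27.1%, leaving 183 × 0.729 = about 133

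**6. Values discarded.** Suppose instead that 15% drop out permanently, 5% before each of T1, T2 and T3 (also an assumption). Participants with all visits: 183 × 0.85 = about 156. Participants with at least one follow-up value: 183 × 0.95 = about 174. About 18 people then have follow-up data that the repeated-measures ANOVA ignores.

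**The case against.** The best defence is that the conflict depends on silence. The article nowhere says that only complete cases will be analysed. Data Availability refers to a full protocol, and an analysis plan may exist. Either could specify imputation before the ANOVA. An absent imputation rule alone would not be a finding. But the article goes further: it names a procedure that excludes incomplete participants and offers an intention-to-treat provision that does not include them. A further document would have to supplement what is written here. The conclusion is therefore conditional on no imputation, and it stands for the text as it is.

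Some stronger readings are tempting, but the documents do not support them.

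- **A reader might infer that the trial's whole analysis is complete-case.** The chi-square tests, which would serve recurrence and readmission, and the one-way ANOVA do not need all visits. If the one-way ANOVA is run at each visit, T1 and T2 values of later dropouts are used there.
- **A reader might infer that deletion costs power, from 87% to 80%.** Those are one-way ANOVA powers, not powers of the repeated-measures test. About 80% at 52 to 53 per group is what the inflation to 61 was meant to preserve. A mixed model would not restore 87% at T3 either, because missing T3 values stay missing.
- **A reader might infer that only loss completely at random avoids bias.** That is too strong: loss that depends on arm alone leaves the mean within each arm unbiased. Loss driven by deterioration during follow-up generally does not.
- **A reader might infer differential loss because the trial is unblinded.** Randomization and blinding says that patients, data collectors and statisticians are blinded and that only intervention practitioners are not. All arms also have home assessments and a gift at each follow-up. The argument rests on the rule that ends participation, not on blinding.

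**Conclusion.** The point holds for the longitudinal comparison of normally distributed outcomes. As written, and with no imputation stated, it is a complete-case analysis and does not match the intention-to-treat statement. The main harm is possible bias from outcome-related loss, together with discarded T1 and T2 values.

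The sample size leaves room for 13% loss (24 of 183). With 5% to 10% missing each follow-up visit independently, 14% to 27% would be excluded, so deletion could exceed that room. The rates are assumed, and missed visits that cluster in the same people would exclude fewer.

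The bias argument assumes that ending participation also ends outcome assessment, which the article does not spell out. The size and direction of any bias cannot be calculated from the article.

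**What to change.** Replace the repeated-measures ANOVA with a likelihood-based linear mixed model, available as MIXED in the SPSS software already named:

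- Include all available visits of all randomised participants, in their allocated group.
- Take the T1, T2 and T3 values as the response, with group, time, group×time and the baseline value as fixed effects.
- Use an unstructured covariance over visits. Mauchly's test and the Greenhouse-Geisser correction are then not needed.

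Multiple imputation before the planned ANOVA, with the imputation model and pooling stated, is an acceptable alternative.

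The mixed model assumes data missing at random, and a participant with no follow-up value adds nothing to it. So add one delta-adjusted sensitivity analysis in which the missing outcomes of dropouts are made progressively worse, and state the range of delta in advance. Keep the recording of reasons for withdrawal, which helps to judge that range. Which visit carries the primary contrast is a separate decision and is not settled by this change.

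The cost is revised wording and slightly more programming. No further patients, visits or software are needed. The change should be made before outcome data are seen, because it determines who enters the comparison.
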